### Additional consent provisions for collection and use of participant data and biological specimens {26b}

Biological specimens are not collected in this project. As of this time, there are no additional studies planned using this data. If additional studies are to be conducted that are not covered here, we would need to get updated consent forms.

## Interventions

### Explanation for the choice of comparators {6b}

Parenting interventions have been widely adopted in Norway to prevent violence towards children, to reduce child problem behaviors and promote positive parenting. The use of these interventions for families with refugee backgrounds is seen as a way to improve the integration process according to the immigration, integration, and child protection authorities in Norway. Both IY and ICDP are widely adopted throughout the country, but neither intervention has been evaluated for effectiveness for this population within Norway. Measurement feedback (MFS) is seen as a new way to improve treatment throughout a variety of mental health fields, though this trial is the first to evaluate an MFS for this population. In 2018, the national strategy for parental support in Norway was established: “Safe parents - safe children” The Government’s strategy for parental support (2018–2021) [18]. Based on this strategy, it has been decided that parent training programs are considered a mandatory part of the welcome/introduction program for refugees in Norway. Several programs have been identified for this use; the minority version of ICDP and the IY Basic Parenting programs are among those named in the report [19].

### Intervention description {11a}

The parenting interventions (factor 1) are both implemented as manual-based programs by their official program providers. Both IY and ICDP have extensive documentation which describes the length of the interventions and the contents of intervention meetings. Furthermore, over the course of intervention, data are collected from interventionists that document the content covered for each meeting session with the parents. The IY intervention in the PIRM-study is The School Age Basic Parenting program, which is conducted over 15 weeks with 3-h weekly meetings involving either one or both parents in a group-based setting. This program aims to “strengthen the parent-child interactions and attachment, reduce harsh discipline and foster parents’ ability to promote children’s social, emotional and academic development” (http://www.incredibleyears.com/programs/parent/school-age-basic-curriculum). This again aims to “prevent, reduce, and treat aggression and emotional problems in young children 0 to 12 years old” (http://www.incredibleyears.com/about/incredible-years-series/). The core components include content and process components. The core content components are as follows: positive parental attention, quality time with children, and sensitive responding to support the children’s development and a trusting relationship between parents and children. Development of predictable routines, positive limit setting, and handling of misbehavior are also important components. The content of the meeting is structured in different process core components with the collaborative process as the main element. Other process components are reflection and problem solving, short video vignettes of child-parent interactions, roleplays to practice skills learned, and home activities to enhance and generalize skills and knowledge developed in the group [20].

The minority version of the ICDP is conducted over 12 weeks with weekly meetings in 2 h sessions in a group-based setting. The program is intended to “support competence of care in parents and others who care for children in their profession” and “aims primarily to influence the quality of contact and the relationship between the child and the caregiver” (Children, Youth and Family Directorate, 2016, p. 15) [21]. The main goals of ICDP are as follows: (1) to promote the positive perception of the child, (2) to influence the caregiver's understanding of how important the interaction between the caregiver and the child is for the child's development, and (3) to promote the caregiver’s perception of herself/himself as a competent caregiver. ICDP consist of 5 core components: (1) caregivers perception of the child, (2) eight guidelines for good interaction with the child, (3) seven principles for sensitization used by a facilitator in relation to the caregiver, (4) six principles for implementation in meetings and in daily practice, and (5) adaptions to different groups and context. The content of the meetings is structured in different themes consisting of caregivers’ perception of the child and the eight guidelines for good interaction with the child. Home activities for the parents, short video vignettes, and roleplays to practice skills learned are used to stimulate reflection and discussion in the group.

The MittEcho feedback system (MFS; factor 2) was developed collaboratively for use in first-line, low threshold services. MittEcho feedback system consists of an app for entering data and a publication portal for viewing results. The MittEcho app is available in Google Play and Apple App Store. The parents in the MFS condition will answer questions based on their experience with parent training, the Measurement Feedback – Parent Scale questionnaire (see measures) and a self-evaluation of their progress on up to three goals that they choose themselves. Data based on parents’ replies to the app are uploaded and displayed in graphs accessible for group leaders in the MittEcho publication portal, which is stored on a secure data server (TSD). The results are updated weekly, and group leaders are expected to review and make evaluations of intervention progress for the group, as well as individual parents within the group.

### Criteria for discontinuing or modifying allocated interventions {11b}

There are no expected iatrogenic effects of participation. Parents are expected to complete the intervention unless they choose to withdraw.

### Strategies to improve adherence to interventions {11c}

All IY and ICDP group leaders undergo formal training for the interventions delivered by the respective program provider. They are given regular supervision by intervention experts. All group leaders are expected to fill out weekly checklists which ask them to evaluate their progress in the intervention. Group leaders in the MFS condition receive additional training by the members of the research team regarding how to access the MittEcho portal to view parents’ responses. They also receive general advice about how to interpret and act on the feedback for each of the participants and answer questions on the checklists regarding use of MFS. The families who complete the most measurement points for the MFS are entered in a drawing for movie tickets.

### Relevant concomitant care permitted or prohibited during the trial {11d}

Participants are not restricted from receiving other care related to parenting or mental health during the trial period.

### Provisions for post-trial care {30}

There is no expectation that the interventions are harmful to the parents. All of the parents in the study are covered under the Norwegian healthcare system, meaning that they have access to mental health resources should they be required.

### Outcomes {12}

The data will be obtained from parents (quantitative and qualitative), group leaders (quantitative and qualitative), teachers (quantitative), and children (qualitative) using web-based questionnaires at baseline, mid-intervention, post-treatment, and/or at 12-month follow-up. Interviews will be conducted in-person (where possible) to gather in-depth information about the parenting interventions. In addition, routine measurements are conducted weekly with help of the MittEcho app.

#### Quantitative surveys

The primary outcome measures note changes on: child problem behavior with the Eyberg Child Behavior Inventory (ECBI) [22], Parenting Practices Inventory (PPI) [23], and Parent Stress Index-Short Form (PSI/SF) [24] supported by qualitative interviews. The measures are available in multiple languages and evaluate parenting interventions and have been shown to be sensitive to change in families from a variety of contexts. Sum scores of the following scales from the quantitative surveys will be compared for the two factors (factor 1: parenting and factor 2: MFS) at T1 to assess possible baseline differences. Longitudinal analysis will follow and will compare changes in scores from, T1 to T2, T1 to T3, and T3 to T4 to assess differences in change for the two factors.

The ECBI is a well-validated, 36-item questionnaire that is scored by parents on frequency (1 yes or 0 no) and intensity (1 never to 7 always) of their child’s (2–16 years) problem behavior. High frequency scores (which range from 0 to 36) indicate more problem behaviors, while high intensity scores (which range from 36 to 252) indicates more intense problem. ECBI is widely used as a measure of problem behavior in studies of the IY program.

The Sutter-Eyberg Student Behavior Inventory-Revised (SESBI) is a teacher version of the ECBI scale. Like the ECBI, the SESBI is a report of the frequency and intensity of a child’s problem behavior.

The PPI is a survey of parenting behaviors and attitudes that are common for many parents [23]. The PPI consists of several sub-scales, of which we are using appropriate discipline, physical punishment, and monitoring.

The PSI/SF is a 36-item parent self-report of parent stress with 3 subscales (i.e., Parental Distress, Parent-Child Dysfunction, and Difficult Child). The items are rated from 0 strongly disagree to 4 strongly agree [24].

The resilience measure (READ) is a 39-item scale that was “…designed to assess the protective resources of personal competence, social competence, structured style, family cohesion and social resources to understand stress adaptation [25].”

#### Other quantitative measures

The Measurement Feedback - Parenting Scale (MF-PS) was developed to evaluate parents’ experiences in parenting interventions for families with refugee background. The survey is delivered via the MittEcho smartphone app.

The Intervention Goals (IG) are a list of 3 goals that parents choose to work on during the intervention. They then rate their satisfaction with progress on their goals over the course of the parenting sessions using the MittEcho smartphone app. In addition, user data for the use of the app and web-portal will be collected and analyzed.

#### Qualitative interviews

Children will be interviewed using techniques from The Dialogical Communication Method (DCM) [26] and the protocol for International Evidence-Based Investigative Interviewing of Children (NICHD) [27]. The interviews with parents and group leaders will be using semi-structured interview guides. The qualitative analyses are explorative, and in line with Denzin and Lincoln’s [28] description, different analytic strategies will be combined. All interviews will be analyzed using the interpretive research frame with a qualitative cross-sectional analytic strategy. A brief version of the interview guide for all participants is summarized in Table 2.

**Table 2 Tab2:** Brief qualitative interview guide

	Background	Experiences with IY or ICDP	Refection concerning IY and ICDP	Effective components in IY and ICDP
**Parents**	Question about: country of origin, ethnicity, Refugee situation, parenting challenges, moving, resettle, acculturation, level of trust, and challenges as refugees.	Experiences regarding IY and ICDP	Reflection regarding IY and ICDP, support and helps when parenting in new context, and general impression of IY and ICDP	Questions about a group lesson, being parent and using IY or ICDP strategies.
**Children**	Question about a normal day, living in a new country, being a refugee, challenges, and strengths (important to balance the former question)	Question about the parents in Norway and country of origin: compare, identify the difference and giving examples of normal day with the parents	Reflection regarding: When are the parents at their best? Worse? “Wishful thinking”: What should change? What do they miss?	Question about if the parents use the IY and ICDP strategies with the children. “Happy thoughts”: What do the parents do as parents today, that you enjoy?
**IY group leaders**	Question about age, gender, education, years as IY or ICDP	Question about the IY or ICDP experiences.	Question regarding reflection on challenges, Comparison to other working methods, feedback form the families and if IY or ICDP are adequate	Question about what works or does not work in IY or ICDP, descend from the manual, ranking the parts of IY or ICDP from best to least favorite and argue for the ranking
**Video of IY groups**	Videos from IY: Looking for group dimension Individual behavioral Influence of the language interpreter	Looking for adherence to program implementation	Looking for feedback, disturbance, and extraordinary episodes	Consider the videos regarding different components of the manuals

Parent’s interviews will focus on investigating whether there is consistency between parent’s understanding of child rearing, care, and creating a safe environment for children. We also seek to identify children’s coping strategies and adaptation to a new context, as well as their experiences related to migration.

Group leaders’ experiences using MittEcho in this context and with this population will also be explored as part of the qualitative interviews and with particular interest in the usefulness of the system and process of using feedback.

Abductive reasoning will be used to analyze the qualitative interviews. Abductive reasoning is oriented to work from the data towards a theory [29]. As a qualitative research design, it works very well with evaluation of programs to “help increase the influence and impact of evidence-based prevention for population benefit” [30]. The chosen analytical strategies will contribute to the discussion of whether the program works, for whom, and under what conditions [31].

## Participant timeline {13}

### Enrollment

Rolling recruitment will be conducted throughout the course of the study period. Eligible families are identified by the municipalities and invited to attend the study. Families who sign and return the consent to the study office are considered enrolled in the study, where they are assigned a study ID and sent the pre-intervention questionnaire.

### Interventions

Interventions are delivered on a rolling basis, which corresponds to when the participants are recruited. The MFS intervention period overlaps directly with each of the parenting interventions. The IY parenting intervention takes place over 15 weeks, with additional weeks added for holidays as necessary. The ICDP parenting intervention takes place over 12 weeks, with additional weeks added for holidays.

### Assessments

#### Quantitative survey

The surveys are sent to the participants following enrollment in the study at pre-intervention (T1). Assessments are then sent (for parents only) mid-intervention (T2), which is 7 or 8 weeks after the IY groups start and 6 weeks after the ICDP groups start; at post intervention (T3) 15 weeks for IY, 12 weeks for ICCDP; and 1 year follow-up (T4). See Table 3 for a more detailed timeline of enrollment and data collection.

**Table 3 Tab3:**
[figure not shown]
Study timeline

#### Qualitative interview

Interviews for the parents are conducted after the families are finished with the intervention (T3). Interviews for the group leaders are conducted after they have led at least one group to completion (T3). Interviews for the children are conducted after their parents have completed the group (T3 or later).

### Sample size {14}

#### Quantitative

The sample size for the PIRM study is based on a significance level of *p* = .05 and power *β* = 0.80. The expected effect size is Cohen’s *d* = .30 for the intervention groups based on differences between sum scores. In other words, we wish to detect a relatively small difference between enrollment in either of the parenting groups (factor 1) or in the addition of the MFS (factor 2). Based on this values, our aim is to recruit *N* = 360 families, *n* (IY, w/MFS) = 90, *n* (ICDP, w/MFS) = 90 , *n* (IY, no-MFS) = 90, n (ICDP, no-MFS) = 90. The study is powered to detect a relatively small effect size for main effects of either the parenting factor, IY_tot_ = 180 vs ICDP_tot_ = 180; or the MFS factor, MFS_tot_ = 180 vs no-MFS_tot_ = 180. Interaction effects between factors (e.g., IY w/MFS vs ICDP w/MFS) were not included in the power analysis due to the unknown nature of the main effects. With 6 families in each intervention group, the study would need roughly 5 municipalities to run two intervention groups, twice per year for 3 years.

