## Recruitment {15}

### Recruitment of municipalities

Recruitment of families will be conducted at the municipality level. Recruitment of municipalities began in 2019 with written invitations and information meetings which was held by the research staff in different sites all over Norway. An invitation letter was sent to the child and family services and immigrant services via the study coordinator, group leaders or Bufetat. The invitation letter described study aims, project participation, and both interventions. The recruitment process will be ongoing throughout the project period until the target of *N* = 360 families is reached

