## Statistical methods

### Statistical methods for primary and secondary outcomes {20a}

We will conduct analyses in a longitudinal framework, controlling for scores at baseline. For example, to test the primary outcomes of the effectiveness study, we will use linear mixed modeling to assess changes in parenting or child behavior in the different intervention groups while controlling for scores pre-intervention. The analyses will account for independence within the respondents (time as a random effect) as well as group membership, because the randomization to the MFS condition is at the group level. We will also look at interactions between main effects given enough power, for example, between the MFS conditions (factor 2) and the parenting conditions (factor 1).

See the “Outcomes {12}” section for description of qualitative analysis.

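### The 80% power at d = 0.30 for N = 360 reproduces only as an individually randomised, complete-data t-test; it has no allowance for groups of 6 and almost none for loss, so it does not support the power claim, above all for the MFS factor.

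*Protocol article*

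**What the plan says.** Sample size {14}, Quantitative, sets a "significance level of *p* = .05 and power *β* = 0.80", and a Cohen's d of 0.30 on the difference in sum scores. From these it derives 360 families, 90 in each of four cells. It then claims: "The study is powered to detect a relatively small effect size for main effects of either the parenting factor", with 180 IY against 180 ICDP, "or the MFS factor, MFS_tot_ = 180 vs no-MFS_tot_ = 180". The same paragraph fixes the delivery unit: "With 6 families in each intervention group, the study would need roughly 5 municipalities to run two intervention groups, twice per year for 3 years".

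Other sections bear on that claim:

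- **Sequence generation {16a} and Implementation {16c}:** MFS is assigned to whole parenting groups, because a leader's response to the feedback reaches everyone in the group. Families are randomised individually to IY or ICDP. Each site runs one group of each programme at the same time, and one of the two is in the MFS condition.
- **Statistical methods {20a}:** the mixed model controls for baseline scores and accounts for group membership, "because the randomization to the MFS condition is at the group level".
- **Recruitment of municipalities:** recruitment continues "until the target of *N* = 360 families is reached". So 360 is the number recruited, not the number analysed.
- **Trial design {8}:** the last survey (T4) comes 1 year after the intervention ends.

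The document gives no ICC, design effect, loss rate or baseline correlation.

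**The concern.** Clustering is recognised in the randomisation and in the analysis but does not enter the sample size. For MFS the comparison is cluster-randomised. For IY against ICDP the families are randomised individually, and clustering arises only because they are then treated together. Outcomes of families in the same group may be correlated, in which case 180 families in groups of 6 carry less information than 180 independent families.

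Loss is a second gap. The plan foresees dropout and missing data, yet the groups multiply out to exactly 360 with no surplus.

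At stake is how a non-significant result on either factor is read. The protocol expects MFS to improve outcomes and the two programmes to perform alike, and it means to inform policymakers. A reader who takes the 80% at face value could give a null MFS result, or an absence of difference between programmes, more weight than the calculation justifies.

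**Working it through.** **Inputs from the document.** Alpha 0.05 (sidedness not stated), power 0.80, d = 0.30, 180 per level of each factor, 6 families per group. Groups: 5 municipalities × 2 groups × 2 per year × 3 years = 60, and 60 × 6 = 360. Each level of MFS therefore has about 30 groups.

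**Reproducing the printed figure.** For a two-sided two-sample t-test with independent families and complete data, the noncentrality is d × √(n/2).

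- n = 176 per arm (352 in total) gives 80.1%.
- n = 180 per arm gives 81.0%.
- The normal approximation needs 175 per arm (350 in total).
- A one-sided test would need 138 per arm, so it does not reproduce 360.

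The printed number is the plain two-sided calculation, rounded up slightly.

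**Margin left in 360.**

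- Loss with no clustering: 1 − 352/360 = 2.2%.
- Clustering with no loss: the largest affordable design effect is 180/176 = 1.023. With DE = 1 + (6 − 1) × ICC, this allows ICC = 0.023/5, or about 0.005.

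**Power with clustering and loss, no baseline adjustment.** ICC and loss are assumed. With m = 6 × (1 − loss), DE = 1 + (m − 1) × ICC and effective n per arm = 180 × (1 − loss)/DE. The test uses 60 − 2 = 58 df.

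| ICC | Loss | m | DE | Effective n per arm | Power at d = 0.30 |
|---|---|---|---|---|---|
| 0.02 | 0 | 6 | 1.10 | 163.6 | 76% |
| 0.05 | 0 | 6 | 1.25 | 144.0 | 71% |
| 0.05 | 20% | 4.8 | 1.19 | 121.0 | 63% |
| 0.10 | 20% | 4.8 | 1.38 | 104.3 | 57% |

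In the third row, the d detectable with 80% power is 0.37.

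**Adding the planned baseline adjustment.** Suppose d = 0.30 is in raw-score SD units. Adjusting for a baseline score with correlation r then divides d by √(1 − r²), here with the ICC held the same after adjustment. For r = 0.5 this is 0.30/√0.75 = 0.346; for r = 0.6 it is 0.30/√0.64 = 0.375.

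| ICC | Loss | Power, r = 0.5 | Power, r = 0.6 |
|---|---|---|---|
| 0.02 | 0 | 87% | 92% |
| 0.05 | 0 | 82% | 88% |
| 0.05 | 20% | 76% | 82% |
| 0.10 | 20% | 69% | 76% |

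The 80% mark lies inside this table. Which side of it the trial falls on depends on three quantities that the document does not state.

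**The case against.** The strongest reply is that the 57–76% figures do not describe the planned analysis. They include the group effect and the loss but leave out the baseline adjustment that the same model makes. That stands. A reader might infer from the first table that the trial is underpowered. The documents do not support this: with a moderate baseline correlation, power reaches or exceeds 80% in several of the settings shown.

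Four further points stand in part.

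- **The factors differ.** Only MFS is randomised by group, so one clustering penalty should not be read as equally certain for both factors.
- **Site pairing helps.** Both concurrent groups run at one site and are split on MFS as well as on programme. Shared site variation therefore largely cancels in both contrasts. The relevant ICC is the group-within-site one, which may be below 0.05 to 0.10.
- **Loss is softened.** Maximum likelihood or multiple imputation lets partly observed families contribute, gift cards support retention, and loss at 1 year need not apply to the earlier contrasts. None of this restores the full 360.
- **The scale of d is unclear.** Outcomes {12} compares sum scores at T1 and then changes in scores. If d = 0.30 refers to change scores, the gain from baseline adjustment differs from the second table.

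It could also be said that an article condenses a fuller protocol. That does not answer the point: the number reproduces without any allowance, so no fuller text can show a meaningful design effect or loss margin inside it.

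**Conclusion.** The concern holds in a limited form. The printed N is not miscalculated: it is a correct answer for independent families with complete data. On that stated basis, 80% survives only with an ICC of at most about 0.005 or a loss of about 2%, and not both at those limits. The flat power claim is therefore unsupported for a trial delivered in 60 groups with follow-up to 1 year. It is weakest for MFS, with about 30 groups on each side; for IY against ICDP the problem comes only through group delivery.

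The size of any shortfall cannot be fixed from the document. Every figure beyond the t-test match rests on an assumed ICC, loss rate and, where used, baseline correlation. The validity of the planned test is not in question, because the model already accounts for group membership. (Power printed as β = 0.80 is a slip of notation and changes nothing.)

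**What to change.** Keep N = 360 and rewrite the quantitative paragraph of Sample size {14}:

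- Give power, or the d detectable with 80% power, separately for each factor under the planned mixed model with 60 groups of 6.
- State the assumed group-within-site ICC (for example 0.02 to 0.10), the loss rate and the baseline correlation, and show the result over a range of each.
- Say whether d = 0.30 refers to post-intervention scores or to change scores.
- Replace the flat power claim with the resulting figure or range.

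The cost is one revised paragraph. No families are added, and the randomisation and analysis stay as they are. The downside is that the stated power may look less favourable, particularly for MFS.
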